### Outcome measures

#### Primary endpoint

The primary outcome is adherence providing self-tracking data, which is calculated as the total number of participants that completed the study at one year follow-up divided by the number who started using the system at baseline. Secondly, the general adherence rate and individual adherence rates of the chatbot, the quarterly assessments and wearing the health watch are compared. Adherence classifications and a dropout threshold were set up to adequately categorize patient’s adherence (see next section ‘Adherence classification and dropout threshold’). Other measures of adherence will also be explored (i.e., adherence rates per quarter, the success rate (percentage of the tasks that the patients complete correctly)).

##### Adherence classification and dropout threshold

Classifications for low, moderate and high adherence are set up to monitor patient’s compliance with providing lifestyle data. The health watch adherence rate, chatbot adherence rate and quarterly assessment completion rates make one-third of the general adherence rate:

$$general\,adherence\,rate\,=\,\left(adherence\,rate\,PHB\,+\,adherence\,rate\,chatbot\,+\,quarterly\,assessment\,completion\,rate\right)/3$$

The chatbot compliance rate is based on the minimum number of days of data collection necessary to gain insight in habitual intake of commonly consumed food. The minimum number of days of data to be collected to gain insight in habitual intake of commonly consumed food is 2–3 days (of food records, real-time monitoring) [17]. Thus, if a patient fills in at least 50% of the measurements, the minimum number of days is certainly met.

The health watch compliance rate is based on the minimum number of days necessary to gain insight in habitual physical activity and sedentary behavior. Previous studies [16] indicate that 3–5 days of monitoring is necessary to assess habitual PA and for sedentary behavior 5-days of monitoring will provide a reliable estimate. Patients were instructed to wear the PHB for at least 12 h a day on average during measurement weeks. Thus, if a patient wears the watch at least 50% of the prescribed time, the minimum number of days certainly is met.

The quarterly lifestyle assessment completion rate is based on the amount of completed quarterly assessments.

The adherence to providing self-tracking data is evaluated by the researchers every four weeks per patient. The total adherence score is a combined score of the chatbot adherence, activity tracker wear adherence and quarterly assessment adherence. The levels are as follows:Low adherence classification: The patient's adherence is below 50% measured over a 4-week interval.Moderate adherence classification: The patient's adherence is between 50 and 75% measured over a 4-week interval.High adherence: The patient’s adherence is above 75% measured over a 4-week interval.

Patients who have a general adherence rate below 50% will be contacted and stimulated to resume using the system by the research nurse once; if patients did not resume after 1 month they are classified as non-adherent.

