**Methods:**

In a prospective observational trial (*N* = 100), the project investigates usability of and adherence to a monitoring system for multiple lifestyle factors relevant to cardiovascular disease, i.e., daily physical activity levels, dietary habits, mental stress, smoking, and sleep quality. Patients with coronary artery disease, valvular disease and arrhythmias undergoing an elective intervention are asked to participate. The monitoring system consists of a secured online platform with a custom-built conversational interface—a chatbot—and a wrist-worn wearable medical device. The wrist-worn device collects continuous objective data on physical activity and the chatbot is used to collect self-report data. Participants collect self-reported lifestyle data via the chatbot for a maximum of 4 days every other week; in the same week physiological data are collected for 7 days for 24 h. Data collection starts one week before the intervention and continues until 1-year after discharge. Via a dashboard, patients can observe their lifestyle measures and adherence to self-reporting, set and track personal goals, and share their lifestyle data with practitioners and relatives. The primary outcome of the trial is adherence to using the integrated platform for self-tracking data. The secondary outcomes include system usability, determinants of adherence and the relation between baseline lifestyle behaviour and long-term patient-relevant outcomes.

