***Subjective continuous lifestyle monitoring***			
Daily dietary habits and drinking behaviour	Self-report via chatbot based on 24 h food diary	Subjective	2–3 days of food records (preferably at least one weekday and one weekend day) [17]
Daily mental stress levels	Self-report via chatbot based on PANAS-scale (as Ecological Momentary Assessment (EMA) [18])	Subjective	No specific frequency, EMA can be adjusted to the design of the study
Daily sleep habits (quantity and quality)	Self-reported via chatbot based on Consensus Sleep Diary [19]; (additionally objectively via health watch)	Subjective (and objective)	At least 7 days including a weekend day [20] (Sleep diary); (5 nights for health watch [21])

The methods were combined in one scheme with a focus on minimizing patient burden and creating regularity. Therefore, the basis of the scheme consists of seven measurement days (based on the minimum habitual sleep measurement frequency, and this includes all days of the week). These seven measurement days are divided over two weeks (for 3 or 4 days per week (2 or 3 weekdays and 1 weekend day)) per four weeks to minimize the activity of the chatbot per week and include measurement free weeks (pause weeks). The first week of reporting contains four reporting days: Monday, Wednesday, Friday and Sunday. The second week of reporting contains three reporting days: Tuesday, Thursday and Saturday. The reporting weeks will take place every other week. Thus, in one month seven days (one complete week of reporting) of measurements is collected. Patients will be asked to wear the health watch in the weeks the chatbot is active to simplify the scheme. The chatbot and health watch scheme can be found in Table 3.

**Table 3 Tab3:** Continuous lifestyle monitoring scheme: “C” = day the chatbot is active. “Wear health watch” = patient is instructed to wear the health watch during the day (night is optional). In the row below the 'Week number' the days of the week are displayed from Monday (M) to Sunday (S)

Week 1							Week 2							Week 3							Week 4						
**M**	**T**	**W**	**T**	**F**	**S**	**S**	**M**	**T**	**W**	**T**	**F**	**S**	**S**	**M**	**T**	**W**	**T**	**F**	**S**	**S**	**M**	**T**	**W**	**T**	**F**	**S**	**S**
**C**		**C**		**C**		**C**									**C**		**C**		**C**								
Wear health watch							Pause							Wear health watch							Pause						

A description of the monitoring method and frequency of each lifestyle domain is described in the following sections.

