##### Daily dietary habits and drinking habit

Eating habits and drinking habits are measured via the chatbot, for seven days per month (Table 3). Participants will be asked to complete a 24 h food diary. The chatbot will aid in filling in the food dairy by prompting the patients after breakfast, after lunch, after dinner and the following morning to fill in their nutrition intake. Patients are prompted to report on the following morning as well to capture whether the patient has eaten something after dinner and before going to bed.

Daily nutrition intake is based on the Dutch Dietary Guideline of 2015 [23] and the Eetscore Food Frequency Questionnaire (FFQ) [24], and assessed through the following categories: vegetables; fruit; legumes; nuts and peanuts; dairy, cheese and cream; bread, cereal products and potatoes; meat, meat substitutes and egg; fish and shellfish; butter, fat and oil; drinks; salt; soup; sugar and confectionery; cake and pastry, savoury snacks and fast food.

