#### Chatbot

A conversational agent (chatbot), called ‘Caro’, is integrated in the Care-On platform. Caro is represented by a female avatar and is programmed to ask the patients questions to monitor the lifestyle parameters sleep, stress, and nutrition intake.

During a measurement day Caro starts a chat session five times per measurement day: in the morning (sleep and stress), after breakfast (nutrition), after lunch (stress and nutrition) and after dinner (stress and nutrition) and the morning after (nutrition). During onboarding Caro will ask patients to fill in their daily schedule to personalize the chat timers.

If a patient is not able to answer a question directly, Caro will ask again after 30 min. The patient has until the next chat session to answer the questions. If a patient has answered all questions of the chat session the measurement is completed and counted for compliance.

The chatbot is available via the platform on desktop and via the ‘MijnFlowCoach’-application [29] which is installed on the patient's phone during onboarding. An impression is shown in Fig. 3.

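### Reaching 50% does not guarantee the minimum number of data days, because chatbot compliance counts sessions and watch compliance counts pooled hours

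*Protocol article*

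**What the plan says.** The section *Adherence classification and dropout threshold* bases the chatbot cut on food records: "The minimum number of days of data to be collected to gain insight in habitual intake of commonly consumed food is 2–3 days". It then concludes: "Thus, if a patient fills in at least 50% of the measurements, the minimum number of days is certainly met". For the watch it cites 3–5 days for habitual physical activity and 5 days for sedentary behaviour, describes wear of at least 12 h a day on average in measurement weeks, and concludes that "if a patient wears the watch at least 50% of the prescribed time, the minimum number of days certainly is met".

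The units are set elsewhere. The *Chatbot* section states: "During a measurement day Caro starts a chat session five times per measurement day". It defines what is scored: "If a patient has answered all questions of the chat session the measurement is completed and counted for compliance". The dietary section builds one 24 h diary by "prompting the patients after breakfast, after lunch, after dinner and the following morning to fill in their nutrition intake", which is four prompts. Table 3 gives seven chatbot days and two watch weeks per four weeks. *Daily physical activity level* asks for at least 12 h a day in those weeks. The abstract differs: "in the same week physiological data are collected for 7 days for 24 h".

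**The concern.** Each guarantee concerns days, but the quantity scored is sessions in one case and hours in the other. Half the sessions is not half the complete days, and half the hours is not half the days.

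The guarantee is the only reason given for placing the cut at 50%. That cut separates the low class from the moderate class and triggers the research nurse's contact; a patient who does not resume within a month is then classed as non-adherent. If the guarantee fails, a patient can be at or above 50% on a component without the amount of diet or sedentary data that the article says this level secures.

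**Working it through.** **The plan's own claim, counted in whole days**
- Chatbot: 0.5 × 7 = 3.5 days, against a minimum of 2–3. Met.
- Watch: 0.5 × 14 = 7 days, against a minimum of 5. Met.

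So the claim can be reproduced in whole days. That is not the unit scored.

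**Chatbot, in sessions**
1. Measurements per four weeks: 7 days × 5 sessions = 35. Half is 17.5, so 18 sessions (51%) reach the cut.
2. A complete food day needs all four nutrition sessions. A day can hold up to 4 completed sessions (three nutrition, plus the morning sleep and stress session) without being complete. Over 7 days that is 7 × 4 = 28.
3. Guaranteed complete food days for *k* sessions = max(0, *k* − 28).

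| Sessions | Rate | Guaranteed complete food days |
|---|---|---|
| 18/35 | 51% | 0 |
| 28/35 | 80% | 0 |
| 30/35 | 86% | 2 |
| 31/35 | 89% | 3 |

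The 80% row is attainable: a patient who skips every morning-after session completes 4 of 5 sessions daily and has no complete diary.

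This is a worst case. As an illustration only, assume each session is completed independently with probability *p*. A food day is then complete with probability *p*⁴, and complete days follow Binomial(7, *p*⁴).
- *p* = 0.50: *p*⁴ = 0.0625; expected complete days 7 × 0.0625 = 0.44; P(≥2) = 6.6%; P(≥3) = 0.7%.
- *p* = 0.75: *p*⁴ = 0.316; expected complete days 2.21; P(≥2) = 70%; P(≥3) = 39%.

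Real completion will cluster within days and patients, so these are not forecasts.

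**Watch, in hours**
1. Prescribed time: 14 days × 12 h = 168 h. Half is 84 h.
2. Continuous wear: 84 / 24 = 3.5 days, touching as few as 4 calendar days. This is within 3–5 days for physical activity but below 5 for sedentary behaviour. The *Health watch* section allows day and night wear, and no cap on counted hours is stated.
3. Even spread: 84 / 14 = 6 h on each of 14 days. This suffices only if a 6 h day counts as valid, which the article does not settle.

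**Denominator**
Under the abstract's 24 h over the same two weeks, prescribed time is 14 × 24 = 336 h. Wear of 12 h on all 14 days (168 h) scores 100% against 168 h and 50% against 336 h.

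**The case against.** The best defence is that the authors were thinking in whole days, where both claims hold. If partly filled days counted, the chatbot claim would also survive: 18 sessions touch at least 4 days (18/5 = 3.6), and at least 3 days with some nutrition data ((18 − 7)/4 = 2.75). A daily cap of 12 counted hours would spread 84 h over at least 7 days, and a 24 h prescription would put half the time (168 h) on at least 7. Valid-day rules and caps are details that an article may leave to the full protocol, and unbroken 24 h wear is an extreme pattern.

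Much of this is fair, and it limits the finding. It does not rescue the guarantee. The article states its units, sessions and time, and draws an unqualified conclusion from them. Part of a day also fits poorly with a 24 h food diary.

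Some stronger readings are tempting, but the documents do not support them:
- **Sleep.** Table 2 asks for sleep diaries on "At least 7 days including a weekend day", and a reader might infer that 50% can never supply them. But sleep is asked in one morning session a day, 7/35 = 20% of sessions, so a patient at 50% can complete all seven. The 50% argument also makes no claim about sleep.
- **High adherence at 80%.** The classes apply to the combined three-part score, not to the chatbot rate alone.
- **Six-hour days as invalid.** No 12 h valid-day rule is stated; 12 h is given as an average.
- **Unusable data.** Nothing says that a diary lacking only its morning-after entry cannot be analysed.
- **Damage to the primary outcome.** This is defined as completing one year divided by starters, and analysed as continued-use status. Its link to the 50% rule is not explicit.

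**Conclusion.** The point holds in limited form. At the 50% cut, the number of complete 24 h food diaries guaranteed is 0, against the 2–3 claimed; the guarantee starts only at 86–89% of sessions. For the watch, 50% of prescribed time can be 3.5 days, against 5 for sedentary behaviour, although the lower end of the physical activity range is still reached.

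The chatbot result assumes that a complete food day means all four nutrition sessions. The watch result assumes a 168 h denominator and no cap on counted hours per day. What fails is the stated property of the threshold, and with it the reason given for choosing 50%. A different justification for the same cut could be offered. The sample size, which rests on anticipated one-year dropout, is not affected. This should be fixed; it does not threaten the trial's main estimate.

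**What to change.** Delete *certainly* from both statements, then take one of two routes.

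1. **Count days.** Express the chatbot and watch rates as days out of 7 and 14. Define a complete food day (all four nutrition sessions) and a valid wear day. Keep the 50% and 75% cuts and the three-part average. The guarantee then holds for each component rate. It should be stated at that level only, because an average of 50% can hide a component at zero: (0 + 50 + 100)/3 = 50.
2. **Keep the rates and report sufficiency separately.** For each four-week interval, give the proportion of patients who reach the plan's own minimums (2–3 complete food days, 5 watch days).

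Either way, reconcile the abstract's 24 h wear with the 12 h in *Daily physical activity level*, *Health watch* and the classification section, so that there is one wear denominator.

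The cost is modest. Wear time and session completion are already recorded, so this is re-scoring rather than new data collection. Under route 1, adherence may look different in either direction: skipping every morning-after session moves the chatbot rate from 80% to 0%, while skipping only the morning sleep and stress session moves it from 28/35 = 80% to 7/7 = 100%. Route 1 also gives that session no weight, so its completion would need separate reporting. Inclusion began in November 2021 and the four-weekly evaluation drives nurse contact, so route 2 disturbs the running study less.

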#### Secondary endpoints

The secondary endpoints are:Usability (measured using the SUS, the feedback given by the patients during the phone consults with the research nurse, the quarterly questionnaires and the evaluation interview) and the success rate (percentage of tasks that the patients complete correctly)).Predictors of adherence to the lifestyle monitoring system (demographic and disease characteristics, quality of life, self-efficacy, depressive symptoms and anxiety, motivation, stage of change, fatigue, physical fitness, levels of metal stress, use of a goal tracking functionality, perception of system usability and prior experience with technology. Standardized questionnaires will be used for self-report measures and objective ambulatory measures from the lifestyle monitoring system for objective lifestyle measures).The association between lifestyle behaviour at baseline with clinical outcomes will be examined by evaluating patient clinical records (re-hospitalizations related to cardiac disease) and standardized self-report data (quality of life).

The data will be analyzed using multiple regression analysis. An overview of the questionnaires to be complete by the patients per timepoint for the secondary endpoints is shown in Table 5.

**Table 5 Tab5:** Overview of the assessments of the secondary endpoints of the Care-On study

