#### Goal tracking module

The patient has the option to set and monitor monthly goals with the goal tracking module. This module is optional. Default goals for dietary intake and physical activity will be provided based on the Dutch Dietary Guideline of 2015 and Dutch Physical Activity Guideline of 2017 [31]. The default goals for sleep and stress are based on the advice given by the Dutch General Practitioners Associations (in Dutch ‘Nederlands Huisartsen Genootschap (NHG)’) on the ‘Thuisarts’-website [32, 33]. The patient has the option to alter the default goals to fit their personal situation.

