#### Quarterly consults by research nurse and final evaluation

Every quarter the research nurse will contact the patient via phone consultation to ask whether the patient has problems using the system. Secondly, the research nurse will ask for brief feedback on the use of the system. Thirdly, the research nurse will remind the patient to fill in the quarterly assessment when the patient has not completed it yet. At last, the research nurse will ask the patient to report medical events.

Within two weeks after the trial period has ended the SUS will be administered again and a semi-structured interview will be held with the participant to discuss their experience with the lifestyle monitoring system. During the semi-structure interview the following topics will be discussed: their quality of life after intervention, their experience with cardiac rehabilitation and/or cardiac care after intervention, their experience with the Care-On study in general, and their perceived usability of the different functionalities of the lifestyle monitoring system.

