### Sample size calculation and statistical analysis

The sample size is based on the primary objective adherence. Anticipating a dropout rate of 50% at 1 year follow up, 100 patients are needed to estimate this adherence rate with a precision of ± 10% (95% CI = [0.398, 0.601]).

Descriptive statistics will be used to report demographics and baseline characteristics. The primary outcome (i.e., ‘adherence’ based on continued use status at 1-year follow-up) will be analysed as a dichotomous outcome measure. Predictors of adherence status and which factors predict re-hospitalizations related to cardiac disease (i.e., the secondary aims) will be investigated using multiple logistic regression analyses. Predictors continuous outcome measures (e.g., QoL) will be examined using linear regression models. Analysis will be carried out in the statistical software package SPSS (version 24, SPSS Inc.).

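### Goal-tracking use is a predictor of 1-year continued use but has no time window, so use counted over the year is liable to look like a driver of adherence when it is not

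*Protocol article*

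**What the plan says.** All references are to the Protocol article.

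- **Outcome and model.** Sample size calculation and statistical analysis takes the outcome to be "adherence’ based on continued use status at 1-year follow-up) will be analysed as a dichotomous outcome measure". Predictors of that status "will be investigated using multiple logistic regression analyses". No landmark, exposure window or time-varying covariate is mentioned.
- **Predictors.** The list under Secondary endpoints includes "use of a goal tracking functionality, perception of system usability and prior experience with technology".
- **Goal tracking.** The Goal tracking module section says: "The patient has the option to set and monitor monthly goals with the goal tracking module. This module is optional". The module has no row in Table 5 and no baseline measurement.
- **Usability score.** Table 5 places the System Usability Scale (SUS) in the adherence-predictor block, with a mark at baseline and another at the evaluation visit t6. The section on quarterly consults and final evaluation states: "Within two weeks after the trial period has ended the SUS will be administered again".
- **Other repeated scores.** The same block of Table 5 shows SF-12, FitMáx and PSS-10 at baseline and at every visit from t1 to t5.
- **Dropout.** The sample size paragraph reads: "Anticipating a dropout rate of 50% at 1 year follow up".

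**The concern.** A predictor in a logistic model of 12-month status should be known before follow-up accrues, or by a fixed early time that everyone in the model has reached. Goal-tracking use does not meet this condition as described. It can only occur while the patient is using the platform, so the opportunity for exposure lasts exactly as long as the patient stays. A patient who leaves at month 2 has had two monthly opportunities and a completer has had twelve. If use is counted over the year, part of the outcome is built into the predictor.

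The Discussion says the determinants of adherence will serve to improve and personalise the system. A module with no effect on retention could be credited with a strong one and guide the redesign.

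The SUS and the repeated questionnaires raise a lesser question. Table 5 lists post-baseline values under adherence predictors, and the text does not say that only the baseline value enters the adherence model. For the third secondary endpoint, by contrast, the article limits lifestyle behaviour explicitly to baseline.

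**Working it through.** **1. The plan's own figure.** For 50 of 100 patients the exact (Clopper-Pearson) 95% interval is 0.3983 to 0.6017. This agrees with the stated 0.398 to 0.601 apart from truncation of the upper limit. The design anchor of N = 100 and 50% dropout is therefore sound and is used below.

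**2. Inputs.** From the article: 50% dropout at 12 months and N = 100. Assumed, because the article gives no figures: exponential dropout, so the monthly rate is λ = ln 2 / 12 = 0.0578; goal uptake at a constant rate r per active month, independent of dropout (true odds ratio 1); and use coded as ever used during the year.

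**3. Formulas.**
- Completers: p1 = 1 − e^(−12r).
- Dropouts: p0 = {0.5 − [λ/(λ+r)] × [1 − 0.5·e^(−12r)]} / 0.5.
- Odds ratio = [p1/(1−p1)] / [p0/(1−p0)].

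**4. Worked case, r = 0.05.** p1 = 1 − e^(−0.6) = 0.451. λ/(λ+r) = 0.0578/0.1078 = 0.536, and 1 − 0.5 × 0.5488 = 0.7256; their product is 0.389. So p0 = (0.5 − 0.389)/0.5 = 0.222. The odds are 0.822 and 0.286, and the odds ratio is 2.88, although goal use has no effect.

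**5. Range of assumed uptake.**

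| r per active month | p1 (completers) | p0 (dropouts) | Odds ratio under no effect |
|---|---|---|---|
| 0.03 | 0.302 | 0.143 | 2.60 |
| 0.05 | 0.451 | 0.222 | 2.88 |
| 0.10 | 0.699 | 0.378 | 3.82 |
| 0.20 | 0.909 | 0.572 | 7.50 |

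**6. At the trial's size.** Simulation with N = 100 under the same null (4,000 replicates, unadjusted 2×2 comparison) gives:

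| r per active month | Median odds ratio, ever used | False positives at nominal 5% | Median odds ratio, 1-month landmark | False positives, landmark |
|---|---|---|---|---|
| 0.02 | 2.4 | 30% | 0.94 | <1% |
| 0.05 | 2.9 | 68% | 0.98 | <1% |
| 0.10 | 3.7 | 89% | 1.02 | 2% |
| 0.20 | 7.0 | 98% | 0.99 | 4% |

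The landmark analysis counts use in month 1 among patients still active at month 1.

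**7. Table 5 beside the text.** The t6 SUS comes after the 1-year period, so it follows the outcome. Footnote 1 of Table 5 makes FitMáx and PSS-10 part of the periodic assessment, and completion of that assessment is one-third of the general adherence rate. For these two, having a later value is thus itself a component of adherence. Prior experience with technology (MDPQ-16) is measured at baseline only and is not affected.

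**The case against.** The best defence is that Table 5 is a schedule of questionnaires, not a model specification. The repeated measures have other stated uses: SF-12 serves quality of life as an outcome, FitMáx and PSS-10 belong to the quarterly lifestyle assessment, and the t6 SUS serves the usability endpoint. An article may leave the choice of value, and the coding of goal use, to the full protocol or analysis plan. This stands for the questionnaires: what remains there is an ambiguity, not a demonstrated error. It answers less for goal tracking, which has no baseline value to fall back on, while the article itself fixes the outcome, the model and this predictor.

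The size of the bias depends on assumed coding, uptake and dropout shape. Default goals are provided, so uptake may cluster at onboarding, and the bias would then shrink. This also stands. The odds ratios illustrate one natural coding; they do not forecast the result.

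A reader might infer more than the document supports:

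- **That usability is measured only during use or after the outcome.** Table 5 schedules a SUS at baseline.
- **That dropouts cannot be reached, or that half the cohort will lack a final SUS.** The article says neither. Stopping use is not refusing contact, and usability is also captured through quarterly items and nurse calls.
- **That the mechanism is reverse causation.** In the calculation goal start is independent of dropout; unequal exposure time alone produces the association.
- **That a spurious predictor is certain.** It is a risk that depends on how goal use is coded.

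**Conclusion.** The point holds for goal-tracking use. Without a time window, use counted over the year depends on how long the patient stayed and is liable to show a positive association with adherence when none exists. Under no effect the odds ratio is about 2.6 to 7.5 for assumed uptake of 3% to 20% per active month, and about 1 with an early landmark. Only the 50% dropout and N = 100 come from the article; uptake rates, exponential dropout and ever-used coding are assumptions. The direction does not depend on the exact rates as long as some uptake occurs after the start.

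For the SUS, SF-12, FitMáx and PSS-10 the finding is limited to an unstated restriction: the article does not say that only baseline values enter the adherence model. The primary adherence estimate is unaffected. The matter concerns a secondary aim and should be settled before the predictor analysis is run.

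**What to change.** 1. Define goal-tracking use as a goal set within the first 4-week cycle, and fit that model in patients still active at week 4. Alternatively, use a discrete-time dropout model with goal use as a time-varying covariate.
2. State that only baseline SUS, SF-12, FitMáx and PSS-10 enter the adherence model.
3. Report later values, including the t6 SUS, descriptively.

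The cost is analysis wording, provided the platform logs when goals are set (assumed). Patients lost in the first 4 weeks leave the landmark model and are reported descriptively. Under the dropout assumption above that is about 6 of 100 by one month (1 − e^(−0.0578) = 0.056).

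Leave the SUS schedule unchanged. A move to t1 would fail for patients included after their intervention, who are not asked the t1 questionnaires (Table 5, footnote 2). Any later first SUS would lose the one measurement taken at baseline and split a cohort that was already enrolling.
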